### Interim Analysis

Do not do so.

## Observation items and methods

### Observations and information and samples to be collected

The blood and urine test data used in this study will not be newly tested because the data obtained in daily practice will be obtained retrospectively (retrospectively) through electronic medical records.

(Pre-intervention)

- Patient background: age, gender, body mass index, medical history (heart failure, diabetes), how to manage medications at home (family management or self-management), meals at home (self-catering, home delivery, eating out)
- Blood tests: serum albumin level, Na, Cl, K, Mg, aspartate aminotransferase, alanine aminotransferase, eGFR, blood urea nitrogen, red blood cell count, white blood cell count, Hemoglobin level, hematocrit, platelet count
- Urinalysis: urine albumin, urine albumin/creatinine ratio, or urine protein, urine protein/creatinine ratio
- Oral medications: presence or absence of concomitant medications (mineralocorticoid receptor antagonists, renin-angiotensin-aldosterone inhibitors, sodium glucose cotransporter2 inhibitors) that increase serum potassium levels, presence or absence of concomitant medications (loop diuretics) that reduce serum potassium levels, presence or absence of potassium adsorbents
- Vitals: Resting blood pressure (systolic and diastolic) after visiting the station

In addition, if the blood pressure at home is recorded in the blood pressure notebook, it is possible to substitute the resting blood pressure after the visit.

(12 weeks after intervention)

- Patient background: age, gender, body mass index, medical history (heart failure, diabetes), how to manage medications at home (family management or self-management), meals at home (self-catering, home delivery, eating out)
- Blood tests: serum albumin level, Na, Cl, K, Mg, aspartate aminotransferase, alanine aminotransferase, eGFR, blood urea nitrogen, red blood cell count, white blood cell count, Hemoglobin level, hematocrit, platelet count
- Urinalysis: urine albumin, urine albumin/creatinine ratio, urine protein, urine protein/creatinine ratio
- Oral medications: presence or absence of concomitant medications (mineralocorticoid receptor antagonists, renin-angiotensin-aldosterone inhibitors, sodium glucose cotransporter2 inhibitors) that increase serum potassium levels, presence or absence of concomitant medications (loop diuretics) that reduce serum potassium levels, presence or absence of potassium adsorbents
- Vitals: Resting blood pressure (systolic and diastolic) after visiting the station

In addition, if the blood pressure at home is recorded in the blood pressure notebook, it is possible to substitute the resting blood pressure after the visit.

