# Shema

- Main eligibility criteria: Patients with an estimated glomerular filtration rate (eGFR) of less than 45 mL/min/1.73 m2 who attend the Mie Chuo Medical Center of the National Hospital Organization
- Timing of patient registration: The first day of the patient's visit to the pharmacy of the cooperating facility during the enrollment period
- Number of cases and registration period: 40 people, December 2022 ~ February 28, 2023
- Intervention Methods:

1. Questionnaire survey on awareness of the intake of potassium-containing foods

2. Dietary guidance: Nutritional guidance using explanatory documents on diet

3. Measurement of resting blood pressure after visit

4. Sharing information on the status of potassium adsorbents with Mie Chuo Medical Center

- Follow-up period: 3 months (after 84 days) from the first day of intervention

Study design

- positive
- Intervention Studies
- Design features: Before-and-after comparison test, open design
- Contrast Type: None
- Facility: Multi-center
- Randomization: No
- Level of Blinding: Open-label

[figure not shown]

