### Secondary Objectives

| Secondary Objectives | Evaluation items | Reasons and Validity for Selection of Evaluation Items |
| --- | --- | --- |
| Change in Attitudes Toward the Intake of Potassium-Containing Foods | Survey Results | Evaluated on a 5-point scale for questions about awareness of potassium restriction |
| Change in resting blood pressure before and after intervention | Systolic and diastolic blood pressure at rest at visit | Blood pressure fluctuations are expected due to diet |

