### Statistical analysis

(1) Primary endpoint

The mean and standard deviation of serum potassium levels before and after the intervention will be calculated, and a paired student's t-test will be performed at 5% on both sides of the significance level.

(2) Secondary endpoint

The mean and standard deviation of resting blood pressure before and after the intervention will be calculated, and a student's t-test will be performed with a significance level of 5% on both sides. For the content of the questionnaire, Fisher's exact test or chi-square test will be performed at a significance level of 5% on both sides of the change in awareness of potassium limitation.

(3) Comparison of patient backgrounds

Nutritional guidance will be used to compare the patient's background between the improved and non-improving serum potassium groups. For the nominal variables of gender, medical history, medication administration at home, and eating at home, Fisher's exact test or chi-square test is performed at 5% on both sides of the significance level. For the continuous variables age, Body mass index, and eGFR, the mean and standard deviation are calculated, and a student's t-test is performed with a correspondence of 5% on both sides of the significance level.

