### Observation and Reporting Schedule

| item | Prescription Fulfillment  (Start of observation) |  |  | End of Observation Period |
| --- | --- | --- | --- | --- |
| Number of days elapsed since obtaining consent | Day1 |  |  | Day 84 onwards* |
| Obtaining Consent | 〇 |  |  |  |
| Questionnaire for awareness survey on the intake of potassium-containing foods | 〇  (Questionnaire 1) |  |  | 〇  (Questionnaire 2) |
| Nutritional Guidance on Potassium Restriction | 〇 |  |  | 〇 |
| Follow-up on Nutrition Guidance |  | 〇 | 〇 |  |
| Patient Background Verification | 〇 |  |  | 〇 |
| Checking blood test data | 〇 |  |  | 〇 |
| Confirmation of urinalysis data | 〇 |  |  | 〇 |
| Confirmation of oral medication | 〇 |  |  | 〇 |
| Measurement of resting blood pressure after the visit | 〇 | 〇 | 〇 | 〇 |
| Confirmation of adherence of potassium adsorbents | 〇 | 〇 | 〇 | 〇 |

*The date of data acquisition after 84 days after obtaining consent depends on the date of the patient's outpatient treatment, so it shall be after Day 84.

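### Resting blood pressure is tested before and after the guidance, but several antihypertensive classes and all antihypertensive doses go unrecorded, so those treatment changes cannot be separated from an effect of diet

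*Protocol*

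**What the plan says.** Section 2.1.2 (Secondary Objectives) lists systolic and diastolic resting pressure and justifies the choice with "Blood pressure fluctuations are expected due to diet". Section 8.2 names lower resting blood pressure among the benefits expected from the guidance. Section 3.5.2(2) fixes the analysis: "The mean and standard deviation of resting blood pressure before and after the intervention will be calculated, and a student's t-test will be performed", two-sided at 5%. The Shema gives the design as "Design features: Before-and-after comparison test, open design", with no comparator.

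Section 3.6.1 has a list of medicines before the intervention and the same list at 12 weeks. Both are organised by effect on potassium. The first group holds three classes that raise it: mineralocorticoid antagonists, inhibitors of the renin-angiotensin-aldosterone system and SGLT2 inhibitors, each noted only as taken or not. The remaining entries are "presence or absence of concomitant medications (loop diuretics) that reduce serum potassium levels, presence or absence of potassium adsorbents".

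No dose is requested and no other antihypertensive class is named. The schedule in section 3.6.2 has a row "Confirmation of oral medication", marked at Day 1 and at the end of observation, without further content. The eligibility criteria (4.1.1 and 4.1.2) do not ask for stable antihypertensive treatment. The statistical section uses no drug variable: the background comparison in 3.5.2(3) covers "For the nominal variables of gender, medical history, medication administration at home, and eating at home", plus age, body mass index and eGFR.

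**The concern.** With no control group, a treatment change between the two readings is not balanced by anything. It can be taken into account only if it is recorded. The list in 3.6.1 suits the potassium endpoint, but it was not extended for the blood pressure endpoint.

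The patients have CKD stage G3b to G5, are under outpatient prescription, and have their pressure measured at each pharmacy visit over 12 weeks or more. Some adjustment of antihypertensive treatment in that time is plausible, although the protocol gives no rate. A patient whose unlisted drug is added, or whose dose is raised, would show a fall that looks like a response to the guidance. A patient whose treatment is reduced would hide a response. The planned data would not show which patients these were.

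This cannot be left to a statistical analysis plan, because no analysis can use a variable that was not collected.

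**Working it through.** **What the planned data can and cannot show**

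| Change between the two readings | Visible under 3.6.1? |
|---|---|
| Start or stop of a renin-angiotensin-aldosterone inhibitor, mineralocorticoid receptor antagonist, SGLT2 inhibitor or loop diuretic | Yes, recorded as present or absent at both times |
| Dose change in one of those classes | No, dose is not recorded |
| Start, stop or dose change in an unlisted class (for example calcium-channel blocker, beta-blocker, alpha-blocker, thiazide-type diuretic) | No |

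The medication row in 3.6.2 does not change this table, because 3.6.1 is the only place that says what is to be recorded. The web-form items in section 3.4 ask how medicines are managed at home, not which antihypertensives are taken.

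**The plan's own figure**

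There is none for blood pressure: no SD, expected effect or power is stated. The required n = 34 (goal 40) is for serum potassium and is not affected by this point.

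**Illustration of size**

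Inputs: n = 40 is the protocol's goal. Everything else is assumed: k = 4, 6 or 8 patients with an unrecorded addition or increase, a fall of e = 8 or 10 mmHg in each, SD of change 12 mmHg, no effect of diet, all changes in the same direction, and a paired test.

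- Mean shift = (k/40) × e
- Standard error = 12/√40 = 1.90 mmHg
- Chance of a significant result = two-sided 5% paired t-test power (noncentral t, 39 degrees of freedom) at that shift

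| k of 40 | Mean fall, e = 8 | Mean fall, e = 10 | Chance of p < 0.05 |
|---|---|---|---|
| 4 | 0.8 | 1.0 | 7.0% to 8.1% |
| 6 | 1.2 | 1.5 | 9.5% to 12.0% |
| 8 | 1.6 | 2.0 | 13.0% to 17.7% |

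The largest case, 2.0/1.90, is about one standard error.

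A wider set of assumptions gives the outer range. With 5% to 30% of patients changing, 5 to 10 mmHg each and an SD of 10 to 15 mmHg before the spread caused by the drug changes is added, the shift is 0.25 to 3.0 mmHg. The chance of a significant result at n = 40 is then 5.1% to 39%. At the low end this is indistinguishable from the nominal 5%; at the high end it is not.

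**The case against.** A reader might infer that most blood-pressure-lowering drugs are not collected. The documents do not support that. Four classes that also lower blood pressure are recorded at both time points, and there are no prescribing data from which to say what share of treatment is missed.

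A reader might also infer that the blood pressure objective cannot be answered at all. That goes too far. The objective in 2.1.2 is the change before and after the intervention, and the two readings measure that. Only the step from change to diet is weakened. Much of that weakness comes from having no control group: regression to the mean, season and measurement setting (home notebook readings may replace visit readings) are also uncontrolled, and recording more drugs would not cure them. Section 20 itself calls the study exploratory.

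The sizes above are assumptions. Even the worst case in the table leaves a chance of more than 80% of no false signal. Reductions in treatment would offset additions. The protocol has no procedure for reporting blood pressure readings to the prescriber; its tracing report concerns potassium adsorbents.

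Finally, an analysis restricted to patients with unchanged treatment selects on something that happens after baseline. Patients with high readings may be the ones whose drugs are raised, so leaving them out can itself bias the change.

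All of this stands, and it limits the point to unlisted classes and doses and limits what the supportive analysis can bear. It does not remove the gap: a main competing explanation for a tested endpoint is only partly recorded, although the pharmacies already hold the prescriptions.

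**Conclusion.** The point holds in limited form. Section 3.6.1 misses starts and stops in unlisted antihypertensive classes and dose changes in every class. A blood pressure change in this uncontrolled study cannot be separated from those. Starts and stops of the four listed classes can be seen.

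The size of the bias cannot be derived from the protocol. On the assumed inputs the mean moves by 0.8 to 2.0 mmHg, and the chance of a falsely significant result is about 7% to 18% instead of 5%. The bias is negligible if treatment changes are rare and material if they are common, and it can run in either direction. The planned data could not show which case applies.

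This concerns a secondary endpoint only. The potassium endpoint and the sample size are untouched. It is worth correcting because it costs little.

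**What to change.** - **Section 3.6.1, both lists:** add all antihypertensive drugs with daily dose, at Day 1 and at the final visit, taken from the prescriptions the pharmacies already dispense. State in 3.6.2 that the oral-medication row covers these items.
- **Section 3.5.2(2), description:** report how many patients had antihypertensive treatment started, stopped, raised or lowered between the two readings.
- **Section 3.5.2(2), sensitivity analysis:** add the blood pressure change in patients with unchanged treatment. Read it alongside the all-patient result and not in place of it, because the subset is selected on a post-baseline event and still has no control.
- **Wording of conclusions:** describe any blood pressure result as a before/after change, not as an effect of diet, and bring the rationale in 2.1.2 and the expected benefit in 8.2 into line with that.

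The cost is a few extra data fields, one table of counts and one smaller, selected supportive analysis. None of it alters how patients are treated.

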### Observation and Reporting Schedule

| item | Prescription Fulfillment  (Start of observation) |  |  | End of Observation Period |
| --- | --- | --- | --- | --- |
| Number of days elapsed since obtaining consent | Day1 |  |  | Day 84 onwards* |
| Obtaining Consent | 〇 |  |  |  |
| Questionnaire for awareness survey on the intake of potassium-containing foods | 〇  (Questionnaire 1) |  |  | 〇  (Questionnaire 2) |
| Nutritional Guidance on Potassium Restriction | 〇 |  |  | 〇 |
| Follow-up on Nutrition Guidance |  | 〇 | 〇 |  |
| Patient Background Verification | 〇 |  |  | 〇 |
| Checking blood test data | 〇 |  |  | 〇 |
| Confirmation of urinalysis data | 〇 |  |  | 〇 |
| Confirmation of oral medication | 〇 |  |  | 〇 |
| Measurement of resting blood pressure after the visit | 〇 | 〇 | 〇 | 〇 |
| Confirmation of adherence of potassium adsorbents | 〇 | 〇 | 〇 | 〇 |

*The date of data acquisition after 84 days after obtaining consent depends on the date of the patient's outpatient treatment, so it shall be after Day 84.

### Collection and Evaluation of Adverse Event Information

Once every six months, the principal investigator shall report to the head of the clinical research institute (hospital director) the progress of clinical research and the occurrence of adverse events and defects.

## Discontinuation and termination of the study

### Discontinuation of study subjects

In the following cases, a study subject who has consented to participate in the study may be discontinued from the study:

- When the study subject withdraws consent
- In addition, when the principal investigator deems it

In the event of discontinuation, the research subject will be asked whether or not the data can be used until the discontinuation.

### Discontinuation of the entire study

The Principal Investigator shall consider whether or not to continue the research in the following cases.

1 ) When important information about the quality, safety, or efficacy of the research drug is obtained.

2) When there are no more patients to be observed

3) When it is judged that it is difficult to recruit research subjects and it is extremely difficult to achieve the planned cases.

4) When the Medical Research Ethics Review Committee instructs us to change the implementation plan, etc., and it is judged that it is difficult to accept it.

### Termination of study

The study is terminated when the observation period for all enrolled cases has expired and all data have been fixed, and the analysis of the primary endpoint has been completed.

# Selection Policy for Research Subjects

## Eligibility Criteria

### Criterias of choice

- Disease name and diagnostic method: Patients with an eGFR less than 45 mL/min/1.73 m2
- Stage/type: CKD severity classification stages G3b, G4, G5
- Age: 18 years old or older
- Gender: Regardless
- Indicators of general condition: none
- Associated Major Organ Functions: Renal Function
- Written Patient Consent: Required

### Exclusion Criteria

1. Patients who do not agree to participate in this study
2. Patients who have difficulty communicating
3. Patients with hypokalemia (serum potassium level less than 4.0 mmol/L)
4. Patients undergoing maintenance dialysis
5. Patients Bringing Refill Prescriptions
6. Patients taking potassium preparations internally
7. Patients who are not expected to continue to visit the insurance pharmacy in the study for more than 3 months

## Recruitment of research subjects

Patients with an eGFR of less than 45 ml/min/1.73 m2 who bring an outpatient prescription from Mie Chuo Medical Center between December 1, 2022 ~ February 28, 2023 at the insurance pharmacy of the research institution.

## Registration of study subjects

Registration will be carried out using the case registration form. The principal investigator/co-investigator shall fill in the case registration form with background information such as age and gender of the research subject, and indicate that there are no problems with the inclusion and exclusion criteria. After that, the patient registration form will be sent by fax. By registering, you will be given a case number. The case number, along with information that can identify the study subject, will be transcribed into a correspondence table and kept in a strict security. Do not enter information that can identify an individual, such as a name, in the case registration form.

# Basis for the scientific rationality of the study

It has been reported that the amount of potassium excreted in the urine decreases in CKD stage G3b or later6^)^ and the risk of hyperkalemia is high7^).^ In recent years, it has been shown that pharmacists at community pharmacies improved patient outcomes by providing nutritional guidance for hypertension 8) and diabetes mellitus 9) for a few minutes, in addition to conventional medication guidance. Therefore, it is thought that providing nutritional guidance to CKD patients by pharmacy pharmacists may motivate them to follow a diet at home and contribute to the optimization of serum potassium levels.

# Procedures for obtaining informed consent, etc.

Explanatory documents and consent forms will be prepared by the principal investigator. It will be used after obtaining the approval of the Ethical Review Committee and the permission of the head of the research institution. If you want to revise it, apply to the Ethical Review Committee again, obtain approval, and use it after obtaining permission from the head of the research institution.

In this study, explanations and consent will be obtained by pharmacists at the counter of insurance pharmacies of joint research institutes. Specifically, the director of each joint research institute will explain the outline of the study and the data to be acquired using explanatory documents, and obtain consent from the patient himself/herself. Withdrawal of consent shall be made promptly upon request from the patient and with the signature of the consent withdrawal form.

As a general rule, the matters to be explained to the research subjects when receiving informed consent are as follows. However, this does not apply to matters approved by the head of the research institution in response to the opinion of the Ethical Review Committee.

(1) The name of the research and the fact that permission has been obtained from the head of the research institution to conduct the research.

(2) The name of the research cooperating organization pertaining to the research subject, the name of the person who only provides existing samples and information, the name of the organization to which he belongs, the name of all the principal investigators, and the name of the research institution

(3) Purpose and significance of research

(4) Methods of research (including the purpose of use and handling of samples and information obtained from research subjects) ) and period

(5) Reasons for selection as research subjects

(6) Burden on research subjects and anticipated risks and benefits

(7) The fact that the research can be withdrawn at any time even if the person agrees to the conduct or continuation of the research (if it may be difficult to take measures in accordance with the content of the withdrawal from the research subject, etc., that fact and the reason for the withdrawal will be included). ）

(8) The fact that the research subject will not be treated unfavorably by not agreeing to the conduct or continuation of the research or withdrawing the consent.

(9) Method of disclosure of information on research

(10) At the request of the Research Subject, etc., the fact that the research plan and materials related to the research method can be obtained or viewed to the extent that it does not interfere with the protection of the personal information of other research subjects, etc., and the method of obtaining or viewing such materials

(11) Handling of personal information, etc. (including the method of processing and the creation of pseudonymously processed information or anonymously processed information) ）

Collect information collected in the study from electronic medical records or Google Forms. At that time, information that can identify an individual, such as name and address, is deleted, a code is created to identify the research subject in a way that does not have a regularity with the medical record ID, and a correspondence table between the code and the individual research subject is created. The collected information is information that cannot identify a specific individual unless it is checked against the correspondence table, but it is managed as personal information in this research.

(12) Methods of storage and disposal of samples and information

(13) Conflicts of interest related to research funding sources and other research institutions and conflicts of interest related to individual earnings and other research by researchers, etc.

(14) Handling of research results, etc.

(15) Responding to consultations from research subjects and their related parties (including genetic counseling) ）

(16) If there is an economic burden or gratuity on the research subject, that fact and the details thereof.

(17) In the case of research involving medical treatment that exceeds normal medical care, matters related to other treatment methods, etc.

(18) In the case of research that involves medical treatment beyond normal medical care, measures to be taken regarding the provision of medical care to the research subject after the research is conducted.

(19) In the case of invasive research, whether or not there is compensation for the health damage caused by the research, and the details thereof.

(20) If there is a possibility that the samples and information obtained from the research subject will be used for future research that is not specified at the time of obtaining the consent from the research subject, etc., or that it may be provided to other research institutions, that fact and the content envisaged at the time of obtaining consent.

(21) Invasiveness (excluding minor invasions) In the case of research involving interventions, the person engaged in monitoring, the person engaged in the audit, and the Ethical Review Committee will inspect the samples and information related to the research subject to the extent necessary on the premise that the confidentiality of the research subject will be preserved.

